### Trial design

2.1

This clinical trial is a randomized, multi-centre, open-label study that aims to compare the safety and efficacy between afatinib monotherapy and combination therapy with afatinib plus HAD-B1 for the treatment of patients with locally advanced or metastatic EGFR-mutation-positive NSCLC. Participants will be randomized using a ratio of 1:1 into a treatment group (afatinib 20–40 mg/day plus HAD-B1 2 tablets [972 mg/day]) and a control group (afatinib 20–40 mg/day monotherapy) and will be treated for 16 weeks. As treatment continues, follow-up visits will be scheduled at Day 1, week 2, 4, 8, and 16. Physical examination, vital signs, ECOGPS, clinical laboratory examination, tumor marker examination, imaging diagnosis and tumor evaluation, health-related quality of life survey, combined drug confirmation, and abnormal case evaluation are all performed during each visit. Furthermore, for cold-heat pattern identification and genetic search studies, PMRA chip tests and cold-heat pattern identification surveys are performed prior to randomization.

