### Interventions

2.5

Patients in the treatment group will receive of 1 capsule/day of afatinib (20–40 mg/day orally) plus 2 HAD-B1 tablets (972 mg/day, bid orally) while those in the control group will only receive 1 capsule/day of afatinib (20–40 mg/day orally), which may be changed based on the medical judgment of the investigator. The investigator may extend the duration of the drug’s administration. The HAD-B1 tablets used in this trial will be purchased from the Hanpoong Pharmaceutical Co., Ltd. (Seoul, Korea). HAD-B1 is a medical substance containing *Panax ginseng C.A.* (640 mg), *Panax notoginseng Radix* (839 mg), *Cordyceps militaris* (640 mg), and *Boswellia carterii BIRDWOOD* (480 mg) as raw material medicines. In the toxicity assessment of HAD-B1 orally administered to rats for 13 consecutive weeks, the no-observed-adverse-effect-level (NOAEL) for HAD-B1 was determined as 2000 mg/kg/day. The human equivalent dose (HED) was calculated as approximately 320 mg/kg/day, which was about 19 g/day for a person of 60 kg.^[12]^ The dose of HAD-B1 in this clinical trial is approximately 1/20 of that. In the treatment group, when afatinib is removed, HAD-B1 is also removed; however, when afatinib is reduced, HAD-B1 is not reduced.

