### Safety assessments

2.7

During the study period, subjects will be continuously monitored for frequency, severity, and aspect of events of special interests (ESIs). ESIs include paronychia, loss of appetite, diarrhea, stomatitis, cheilitis, rash, acne dermatitis, interstitial lung disease, and severe hepatopathy. The overall safety profile will be evaluated by using safety indicators such as the numbers of abnormal cases and adverse drug reactions, the frequency of significant abnormalities, as well as severities and aspects of abnormalities, physical examination findings, abnormal vital signs, clinical laboratory findings, and clinically significant changes in the ECOG PS scores. The treatment discontinuation rate and reason will be recorded.

In this clinical trial, the “Data and Safety Monitoring Board (DSMB)” will be operated as a safety protection measure for the test subjects. The board will meet every 6 months after the commencement of the study to evaluate the overall safety of clinical trials.

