### Safety assessment

2.11

The number of subjects who will present with adverse events, adverse drug reactions, serious adverse events, and events of special interests, as well as the ratio of those subjects to the total number in the group at baseline, will be recorded. The significance of differences between groups will be tested by using the Chi-Squared test or Fisher exact test. The amount of change at 16 weeks of treatment compared to the baseline for laboratory tests, vital signs, and electrocardiogram (ECG) results will be compared between groups. For continuous variables, descriptive statistics (number of subjects, mean, standard deviation, median value, minimum and maximum values) for the amount of change at 16 weeks of treatment compared to the baseline will be presented, and the statistical significance of differences between groups will be tested by using the paired *t* test or the Wilcoxon signed rank test. While for categorical variables among laboratory tests and ECG results, their frequency will be presented using a contingency table for normal/abnormal changes at 16 weeks of treatment compared to the baseline, and the significance of changes between groups will be tested by using the *t* test, Chi-Squared test, or Fisher exact test.

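### Section 2.11 compares laboratory, vital-sign and ECG data between arms only at week 16, so early or transient abnormalities can be understated in that comparison

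*Protocol article*

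**What the plan says.** Section 2.11 (Safety assessment) states what the arms are compared on: "The amount of change at 16 weeks of treatment compared to the baseline for laboratory tests, vital signs". ECG results are handled in the same way. The continuous summaries repeat the 16-week time point. The categorical laboratory and ECG data go into a "contingency table for normal/abnormal changes at 16 weeks of treatment compared to the baseline". For these three kinds of data the section names no earlier visit, worst value or end-of-treatment value.

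Section 2.1 (Trial design) says that "follow-up visits will be scheduled at Day 1, week 2, 4, 8, and 16". It lists vital signs and clinical laboratory examination among the assessments that, through "abnormal case evaluation are all performed during each visit", are done every time. ECG is not in that list.

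Section 2.5 (Interventions) says that "when afatinib is removed, HAD-B1 is also removed", whereas a reduction of afatinib leaves HAD-B1 unchanged.

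Two other statements limit the point. Section 2.11 reports the number of subjects with adverse events, adverse drug reactions, serious adverse events and events of special interest "as well as the ratio of those subjects to the total number in the group at baseline, will be recorded", with a test between groups. Section 2.7 (Safety assessments) says "subjects will be continuously monitored for frequency, severity, and aspect of events of special interests (ESIs"), includes severe hepatopathy and interstitial lung disease among those events, and has the rate of and reason for discontinuation recorded.

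**The concern.** A comparison at one late time point shows the state of those who are still measured then, at the dose they are then receiving. Two kinds of abnormality can be missed:

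- one seen at week 2, 4 or 8 that has resolved by week 16, for example after a dose reduction;
- one in a patient who has stopped treatment and so has no week-16 value, or only an off-treatment one.

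The first kind matters here because the trial expects exposure to differ by arm: its sample size assumes different rates of keeping the starting dose. A week-16 snapshot would then compare laboratory values under unequal afatinib exposure, and the distortion can run in either direction.

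Laboratory values are also worth using fully because the trial is open-label. Whether an abnormal value is reported as an adverse event depends on an investigator who knows the allocation. The measured value depends on that much less.

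**Working it through.** **Is the week-16 limit a stated choice or only an omission?** It is stated. Section 2.11 names 16 weeks in the general sentence, in the continuous summaries and in the contingency table. Section 2.10.2, by contrast, compares the secondary outcomes at each time point from baseline to week 16. So the article does write multi-visit comparisons in one place and does not do so in Section 2.11.

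**The plan's own figures.** The article gives no figure for this analysis. The nearest is the 10% dropout in Section 2.9, with 71 recruited per group: 71 × (1 − 0.10) = 63.9, which agrees with the stated 64 per group.

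**How many could lack an on-treatment week-16 value?** This is an illustration.

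Inputs: 71 per arm and 10% dropout (Section 2.9); median progression-free survival of 10.94 months on a tyrosine kinase inhibitor alone and 13.50 months with Chinese herbal medicine (another trial, quoted in Section 3). Assumptions: exponential times, dropout independent of progression, and progression ends treatment. 16 weeks = 3.68 months.

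- Dropout alone: 0.10 × 71 = 7.1, about 7.
- Adding progression by week 16, median 10.94: 1 − 2^(−3.68/10.94) = 20.8%. Then 1 − (1 − 0.208)(1 − 0.10) = 28.7%, and 0.287 × 71 = 20.4, about 20.
- The same with median 13.50: 1 − 2^(−3.68/13.50) = 17.2%. Then 1 − 0.828 × 0.90 = 25.5%, about 18.
- Counting only progression by week 8 (1.84 months), median 10.94, because progression found at the week-16 visit would still leave an on-treatment value: 11.0%. Then 1 − 0.890 × 0.90 = 19.9%, about 14.

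The range is 7 to 20 of 71 per arm. Progression makes up most of the upper figure and is not toxicity.

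**How many could be off their starting dose?** Section 2.9 assumes that 57.6% and 80.0% keep it. The complements are 42.4% × 71 = 30.1 and 20.0% × 71 = 14.2, so about 30 against 14 patients. These include dose-reduced patients, who may still have a week-16 value.

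**Direction and possible size of the understatement.** The article gives no abnormality rate or toxicity-stopping rate, so the rates here are assumed. Let p be the true on-treatment abnormality rate. Let a share f of affected patients stop before week 16 and have no value then, while unaffected patients stay. The week-16 rate is p(1 − f)/(1 − pf). With p = 10% against 20%:

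| f | Week-16 rates | Difference (points) |
|---|---|---|
| 0 | 10.0% v 20.0% | 10.0 |
| 0.25 | 7.7% v 15.8% | 8.1 |
| 0.5 | 5.3% v 11.1% | 5.8 |
| 0.75 | 2.7% v 5.9% | 3.2 |
| 1 | 0% v 0% | 0 |

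With p = 5% against 15%, the 10-point difference becomes 7.9, 5.5, 2.9 and 0 points at the same non-zero values of f. The table takes f as equal in both arms. If f differed by arm, the distortion could go either way.

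**The case against.** The strongest reply is that the week-16 table is one supportive part of a wider safety plan. A reader might infer that the plan misses the toxicity that made patients stop. The documents do not support that: adverse events and events of special interest, severe hepatopathy among them, are tested between arms on the full baseline denominator, and discontinuation and its reason are recorded. Section 2.7 also lists the frequency of significant abnormalities with no week-16 limit. This reply stands, and it confines the point to one comparison. It does not remove the point, because Section 2.7 states no between-arm test for its indicators, and adverse-event counts depend on reporting in an open-label trial.

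A reader might also infer that early stoppers are excluded. The article excludes no one and states no rule for a missing week-16 value. Such a rule may be in the full protocol or analysis plan, which are not shown. It would not by itself bring in abnormalities that resolved before week 16.

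Nor can it be said that the comparison conditions on the very outcome HAD-B1 is meant to change. The primary hypothesis concerns keeping the starting dose, and a dose-reduced patient can remain on treatment to week 16.

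Finally, the figure of 20 of 71 is soft. It borrows a median from another trial, applies a control-type value to both arms, and treats dropout and progression as independent although dropout is not defined. It serves only as an upper illustration.

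**Conclusion.** The point holds in a limited form. As written, Section 2.11 makes its between-arm comparison of laboratory, vital-sign and ECG data at week 16 only. That comparison can understate abnormalities that were transient or that occurred in patients without an on-treatment week-16 value. Events reported as adverse events, and reasons for stopping, are still captured elsewhere.

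About 7 to 20 of 71 patients per arm could lack such a value under the assumptions shown. This counts possibly missing values and does not measure bias. With no toxicity-stopping rate in the article, the size of the bias is unknown. The weakness is worth correcting because the correction is cheap, but it does not undermine the safety plan as a whole.

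**What to change.** In Section 2.11, add for all treated patients:

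- a between-arm comparison, by chi-square or Fisher's exact test, of the shift from baseline to the worst post-baseline on-treatment value at scheduled visits, for laboratory tests and vital signs, and for ECG where recordings exist;
- change from baseline by visit;
- time on treatment by arm, shown next to these tables.

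Keep the week-16 change as a supporting table. Put unscheduled values in a sensitivity table, because in an open-label trial the number of unscheduled tests may differ by arm.

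The cost is small. For laboratory tests and vital signs at scheduled visits, the data are already collected under Section 2.1. There is extra output, and abnormality limits must be set for vital signs, which the article does not give. Worst-value rates rise with time on treatment and with the number of measurements, so an arm that stays on treatment longer can look worse for that reason alone. This is why exposure should be reported alongside.

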#### Analysis of second outcome variables

2.10.2

We will compare and evaluate the following between the treatment group and the control group at each time point from the baseline (0 week) to 16 weeks: Progressive survival period (PFS), the time to progression (TTP), and the overall survival rate (OS) present descriptive statistics (number of subjects tested, mean, standard deviation, median, minimum and maximum) and compare statistical significance through Kaplan–Meier analysis. The frequency and percentage of changes in objective response rates (ORR), QOL (EORTC QLQ-C30, EORTC QLQ-LC13, EQ-5D) according to RECIST 1.1 will be presented, and the statistical significance of differences between groups will be analyzed using Chi-square test or Fisher’s exact test.

The reduction of tumor size and tumor markers present descriptive statistics by dose group (number of subjects, mean, standard deviation, median, minimum, and maximum), and statistical significance of differences between groups is to be analyzed by two-sample-test or Wilcoxon signified rank test.

The statistical significance of the variation within each group is tested as either a paired *t*-test or a Wilcoxon signed rank test.

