#### Exploratory outcome variables

2.10.3

We will explore whether treatment reaction and prognosis vary according to cold-heat pattern predisposition. For categorical variables, the frequency and the percentage for each administration group will be presented, and the statistical significance for the differences between groups will be tested by using the Chi-Squared test or Fisher exact test. For continuous variables, descriptive statistics (number of subjects, mean, standard deviation, median value, minimum, and maximum values) for each group will be presented, and the statistical significance of differences between groups will be tested by using the two-sample *t* test or Wilcoxon signed rank test.

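### Section 2.11 assigns only paired tests (paired t, Wilcoxon signed rank) to between-arm differences in continuous safety variables, although the arms are independent; 2.10.2 and 2.10.3 misname only the non-parametric alternative

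*Protocol article*

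**What the plan says.** Section 2.11 (Safety assessment) first sets the comparison: change from baseline to week 16 in laboratory tests, vital signs and ECG "results will be compared between groups". For the continuous variables it then states "and the statistical significance of differences between groups will be tested by using the paired"; the test so introduced is the paired t, and the signed rank test is given as its non-parametric alternative. No other test is offered for them. For normal/abnormal shifts in laboratory and ECG results it says "the significance of changes between groups will be tested by using the" t test, chi-square test or Fisher exact test.

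Two other sections bear on the same choice:

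- Section 2.10.2, for tumor size and tumor markers: "statistical significance of differences between groups is to be analyzed by two-sample-test or Wilcoxon signified rank test". A separate sentence follows for change inside an arm: "The statistical significance of the variation within each group is tested as either a paired" t test or a Wilcoxon signed rank test.
- Section 2.10.3, for continuous exploratory variables: differences between groups are tested by the two-sample t "test or Wilcoxon signed rank test".

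Section 2.1 describes the design: "Participants will be randomized using a ratio of 1:1 into a treatment group" and a control group. No section describes matching of patients across arms.

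**The concern.** The paired t test and the signed rank test both work on differences formed inside a pair, such as the same patient before and after treatment. Patients in two parallel arms are different people and form no pairs. For the continuous variables of section 2.11, both named tests belong to the wrong class, so the section contains no valid test for the comparison it announces.

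Safety is one of the two stated purposes of the trial, and the trial is open-label. An analyst who follows 2.11 literally meets an error message, a p-value that depends on row order, or a within-arm result under a between-arm label. An analyst who notices the problem must choose another test after the data are in. It is better to settle this in the text beforehand.

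**Working it through.** **Inputs.** From the article: parallel arms, 1:1 (2.1); 64 per arm before dropout, 10% dropout, 71 per arm recruited (2.9). Simulated values are standard normal changes chosen for illustration; the article gives no means or SDs for these variables.

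**The plan's own figure.** No stated figure is in dispute here. The 64 per arm reproduces from the two proportions in 2.9 if a two-sided 5% level and 80% power are assumed (the article states neither): 7.849 × (0.576 × 0.424 + 0.80 × 0.20) / 0.224² = 7.849 × 0.4042 / 0.0502 = 63.2, rounded up to 64. It rests on the dose-maintenance rates and does not involve the tests in question.

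**Test against question, section by section.**

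| Section | Variables | Parametric test for between-group difference | Non-parametric test for between-group difference |
|---|---|---|---|
| 2.11 | continuous laboratory, vital signs, ECG | paired t: wrong | signed rank: wrong |
| 2.10.2 | tumor size, tumor markers | two-sample test: valid | signed rank (misspelled): wrong |
| 2.10.3 | continuous exploratory | two-sample t: valid | signed rank: wrong |

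This holds in 2.10.3 whether its groups are treatment arms or cold-heat patterns, since either way they are different patients.

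**What happens if 2.11 is followed literally.** There are three possibilities.

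1. *Unequal evaluable arms.* With 64 and 61 values, both paired procedures return an error and no p-value exists. This is the likely case. If each of 71 patients per arm is independently evaluable with probability 0.90, the chance of equal counts is the sum over k of P(k)², with k binomial(71, 0.90). That is 0.112, so the arms differ in size with probability 1 − 0.112 = 0.89. With evaluability of 0.85 or 0.95 the figure is 0.91 or 0.84.

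2. *Equal arms, paired arbitrarily.* The paired t statistic divides the mean difference by √[(s₁² + s₂² − 2·r·s₁·s₂)/n], where r is the chance correlation created by whichever row order is used. The two-sample t statistic has no r. For one simulated data set (64 per arm, true difference 0.4 SD), over 2,000 random pairings:
   - paired t: p from 0.001 to 0.030; two-sample t: p = 0.0096
   - signed rank: p from 0.0005 to 0.057; rank-sum: p = 0.0072

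   The signed rank result crosses 0.05 on row order alone. Averaged over repeated trials with no true difference, the arbitrarily paired t test rejected in 5.2% of 10,000 runs, the same as the two-sample t test (5.2%).

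3. *Paired test run inside each arm.* With both arms truly changing by 0.4 SD and no difference between them (64 per arm, 5,000 runs), a given arm was significant in 88.8% of runs and exactly one of the two arms in 19.8%. The two-sample t test rejected in 5.0%. A significant and a non-significant arm side by side can therefore suggest an arm difference that is not there.

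**The case against.** The strongest reply is that this is loose wording. The article garbles other technical terms (the Fisher test in 2.10.1, the signed rank test in 2.10.2), and in 2.10.2 and 2.10.3 the signed rank test stands next to a two-sample test, which suggests that the rank-sum test was meant. Section 2.10.2 also gives within-group change its own sentence, so the authors know the two questions apart. For those two sections the reply largely stands: a copied mislabel explains the text at least as well as a planned misuse, and a usable two-sample test is already named. It does not rescue 2.11, where both named tests are paired and the text says twice that the comparison is between groups. Nor is this detail left to a statistical analysis plan, because the article itself names the tests.

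A reader might also infer more than the text supports:

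- *That the trial's between-arm comparisons in general rest on paired tests.* They do not. The primary outcomes, the objective response rate and the adverse-event comparisons use chi-square or Fisher tests, and PFS, TTP and OS use Kaplan-Meier analysis.
- *That false positives would be inflated throughout.* With equal arms and arbitrary pairing, the paired t error rate stays near nominal. With unequal arms the test fails visibly. The high within-arm rejection rate in the third case follows from the assumed true change and is not a between-arm type I error.
- *That the t test listed for categories leaves those data without a valid test.* Chi-square and Fisher stand beside it, so this is a minor slip.

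**Conclusion.** The point holds within a limited scope. In 2.11 the named tests cannot compare independent arms on any continuous laboratory, vital-sign or ECG change. In 2.10.2 and 2.10.3 only the non-parametric alternative is wrong. In 2.11 a t test is also listed, wrongly, for normal/abnormal data. The harm is a p-value that cannot be computed, is arbitrary, or answers a within-arm question; it is not a uniform rise in false positives.

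This should be fixed, but it does not threaten the main conclusions, since the primary outcomes, sample size and adverse-event comparisons are untouched. The conclusion rests on the article's wording and on the absence of any described matching. The simulated figures illustrate the mechanism under assumed normal changes and do not predict the size of error in this trial. The 0.89 probability of unequal arms assumes independent loss at the article's 10% rate.

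**What to change.** Change the wording in three places:

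- **2.11, continuous variables:** test between-arm differences in change from baseline with the two-sample t test or the Wilcoxon rank-sum (Mann-Whitney) test.
- **2.10.2 and 2.10.3, continuous variables:** keep the two-sample test (naming it the two-sample t test in 2.10.2) and replace the signed rank test with the rank-sum test as its alternative. Keep the paired t and signed rank tests only for change within an arm.
- **2.11, normal/abnormal categories:** delete the t test and leave chi-square or Fisher.

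Nothing further is needed to cure the defect. A baseline-adjusted model would be an optional refinement. The cost is an edit to the text; no patients, data or sample-size change are involved. It should be made before the data are analysed, because the trial is open-label and a later choice of test could be questioned.
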